**Objective:**

This prospective study aims to measure the prevalence of ventricular arrhythmias in patients with HCM observed by mobile health (mHealth)–based continuous rhythm monitoring over 14 days compared to standard practice (a 24- and 48-h long-term ECG). The frequency of ventricular arrhythmias in this 14-day period is compared with the frequency in the first 24 or 48 hours for the same patient (intraindividual comparison).

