## Methods

### Study Design

The Hypertrophic Cardiomyopathy: Clinical Impact of a Prolonged mHealth-Based Arrhythmia Monitoring by Single-Channel ECG (HCM-PATCH) study aims to investigate the association between the occurrence of cardiac arrhythmias with detected gene mutations and the extent of late gadolinium enhancement in cMRIs. This single-center prospective cohort study will be conducted at the Department of Cardiology and Intensive Care Medicine at the University Hospital Ostwestfalen-Lippe (OWL), Campus Klinikum Bielefeld in Germany. The trial is registered under clinical trial number DRKS00032144 (DRKS-ID).

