### Statistical Analysis

The sample size has been planned in collaboration with the Department of Biostatistics and Medical Biometry at the Medical School OWL, Bielefeld University. Patients should be divided into low- or intermediate-risk groups according to their HCM Risk–SCD calculator score, and both groups should be of equal size. Based on the prevalence of nsVT, an assumption was made for the group of low-risk patients based on the publications of Magnusson and Mörner [16] and Sakhi et al [17], where the prevalence after a 24- to 48-hour long-term ECG ranged from 7% to 42%. For case-finding purposes, the assumption was made that a similar increase (ie, a doubling) would be expected after 14 days in the intermediate-risk group. Therefore, a prevalence of 25% after 14 days is assumed. In the intermediate-risk group, a prevalence of 75% is expected [6]. Using a *χ*^2^ test, the total number of cases is 30, corresponding to 15 patients per group (α=0.05, power=0.8). In addition, a dropout probability of 10% was considered. This would result in 34 cases (17 per group).

After data collection, a statistical analysis will be conducted concerning the primary and secondary end points. Since this is a cohort study, all analyses will be adjusted for confounders, including, for example, age and sex. Potential confounders will be assessed from a clinical point of view before the statistical analysis is performed. A Poisson regression will be applied to analyze the primary end point (rate of nsVT detection). Furthermore, we will conduct a negative binomial regression as a sensitivity analysis. The same will be done for the secondary end points measured as the number of patients that experience specific events during the study period. Secondary end points regarding the prevalence of cardiac arrhythmias will be analyzed using logistic regression.

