## Results

The primary study objective and primary end point is the prevalence of nsVT in patients with HCM at low to intermediate risk (according to the HCM Risk–SCD calculator) and additional mHealth-based prolonged rhythm monitoring. We will also explore the following secondary end points:

Number of patients undergoing a change in therapeutic procedure (ICD, antiarrhythmic drugs, etc) due to detected nsVT in additional monitoringNumber of patients with detection of AF (duration >30 sec) by prolonged monitoringNumber of patients who experience a change in therapeutic procedure (anticoagulation, antiarrhythmic drugs, catheter ablation, etc) due to detected AFPrevalence of cardiac arrhythmias in patients with positive cMRI findings (>5% late gadolinium enhancement)Prevalence of cardiac arrhythmias in patients with positive genetic diagnosis (detection of HCM-typical gene mutations)

Patient recruitment began in June 2023 and is expected to be completed in February 2024. Data analysis has not yet started. An example table listing patient characteristics and outcomes is provided in Multimedia Appendix 2.

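### The stated 80% power belongs to an unpaired low- versus intermediate-risk χ² test that is neither a listed end point nor the planned analysis; the within-patient objective has no stated size or precision

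*Protocol article*

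**What the plan says.** - **Sizing (Statistical Analysis).** Two independent groups of the same size are formed by risk score. For low-risk patients, "Therefore, a prevalence of 25% after 14 days is assumed"; for the others, "In the intermediate-risk group, a prevalence of 75% is expected". With a χ² test, "the total number of cases is 30, corresponding to 15 patients per group (α=0.05, power=0.8". A 10% dropout allowance brings this to 34. The Recruitment section says that this number suffices for the statistical analysis.
- **Objective (Abstract, repeated in the Discussion).** The 14-day frequency "is compared with the frequency in the first 24 or 48 hours for the same patient (intraindividual comparison". The Outcomes section describes the same comparison of the first 24 and 48 hours with the whole period.
- **End points (Results).** "The primary study objective and primary end point is the prevalence of nsVT in patients with HCM at low to intermediate risk", that is, both risk groups taken together. None of the five secondary end points compares the risk groups.
- **Analysis (Statistical Analysis).** The primary end point, here called a detection rate, goes into a Poisson regression adjusted for confounders. The χ² test appears only in the sizing.
- **Study Design.** Here the project "aims to investigate the association between the occurrence of cardiac arrhythmias with detected gene mutations and the extent of late gadolinium enhancement in cMRIs". That aim is not called primary, and the Results section places both of its parts among the secondary end points.

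**The concern.** A sample-size statement should tell the reader how well the study can answer its main question. Here the sized question, whether intermediate-risk patients have more nsVT over 14 days than low-risk patients, differs from the question in the objective, from the listed primary end point and from the planned analysis. The short-window figures enter the calculation only as background to the 25% assumption. The share of patients whose first nsVT appears after the short window, which governs the within-patient comparison, is never considered.

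Two things are at stake. The 80% could be carried over to a 14-day versus 48-hour result that it does not describe. And with the primary end point worded differently in different sections, a pooled prevalence, a rate, a within-patient gain or a risk-group difference could each be reported later as the main result.

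**Working it through.** **1. Reproducing the plan's figure.** Inputs from the Statistical Analysis section: p1 = 0.25, p2 = 0.75, α = 0.05, power 0.80, equal groups. Sidedness is not stated; two-sided reproduces the figure. With pooled variance under the null (mean prevalence 0.5):

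n per group = [1.96·√(2·0.5·0.5) + 0.8416·√(0.25·0.75 + 0.75·0.25)]² / 0.5² = 14.46, so 15 per group and 30 in total.

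Exact power of the uncorrected Pearson χ² test at 15 per group is 80.8%. Dropout: 30/0.9 = 33.3, so 34. Both stated figures reproduce, as an unpaired between-group test.

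**2. Matching the sized contrast to the declared aims.**

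| Place | Comparison or quantity | Is it the sized contrast? |
|---|---|---|
| Objective, Outcomes, Discussion | 14 days versus first 24/48 h, same patient | No |
| Results, primary | nsVT prevalence, both risk groups together | No |
| Results, five secondary | therapy changes, AF, arrhythmias by cMRI or genetic finding | No |
| Statistical Analysis, primary | adjusted Poisson regression of detection rate | No |

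**3. What 30 patients give for the within-patient question at 48 hours.** Inputs:
- Intermediate risk: 34% at 48 h (Introduction) and 75% at 14 days, so an added yield of 75 − 34 = 41%.
- Low risk: 25% at 14 days. The 48-hour value is an assumption: 12.5%, half of 25% under the stated doubling, so an added yield of 12.5%.

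Expected new detections: 15·0.41 + 15·0.125 = 6.15 + 1.88 = 8.03, about 8 of 30 (26.75%).

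The short window lies inside the 14 days, so patients can be discordant in one direction only. With b newly detected patients, the exact two-sided McNemar p-value is 2·0.5^b: 0.0625 at b = 5 and 0.031 at b = 6. Hence b ≥ 6 is needed.

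P(b ≥ 6), with b = Bin(15, 0.41) + Bin(15, 0.125):
- 30 patients: 0.866, about 87%.
- 34 patients (17 per group): 0.935, about 93%.

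**4. Sensitivity.** For a common added yield d and 30 patients, P(Bin(30, d) ≥ 6) is:

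| d | P(b ≥ 6) |
|---|---|
| 25% | 80% |
| 20% | 57% |
| 15% | 29% |
| 10% | 7% |

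The protocol's cited short-window range is 7% to 42%. A low-risk value of 7% gives an added yield of 25 − 7 = 18% and P(b ≥ 6) = 92%. The upper end, 42%, cannot be combined with 25% at 14 days.

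**5. The 24-hour comparison.** The Discussion gives 16.9% at 24 h against 75% at 14 days, an added yield of 58.1%. Using this for the intermediate group and keeping 12.5% for the low-risk group, P(b ≥ 6) is about 99% with 30 patients.

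**6. Precision (exact Clopper–Pearson 95% CI, n = 30).** Added yield 8/30 = 27%: 12% to 46%. Pooled 14-day prevalence 15/30 = 50%: 31% to 69%.

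**The case against.** The strongest reply is that the sizing text hides nothing. It names the two risk groups, both prevalences and the χ² test, and recruitment is planned as 17 plus 17, so a between-group contrast was visibly intended and a fuller document may list it. That is fair as to intent. It does not remove the fault, because this document itself fixes the size, the test, the objective and the end points, and they do not fit together.

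Several stronger readings are tempting and should not be drawn:

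- **That the study is underpowered for its main question.** At the plan's own rates the pooled figures are about 87% (48 h) and 99% (24 h). Within one risk group the 48-hour figure would be lower (63% in 15 intermediate-risk patients, about 1% in 15 low-risk patients), but no section plans such a test.
- **That P(b ≥ 6) is a proper power target.** Longer monitoring cannot detect nsVT in fewer patients than its own first 48 hours, so the McNemar null is hardly a real hypothesis. Precision is the better basis.
- **That three rival primary aims are declared.** The Study Design aim is not called primary. The move between rate and prevalence is partly loose wording: the Introduction itself uses rate for a share of patients.
- **That the Poisson analysis cuts the power for the sized contrast to 42% (Wald) or 54% (likelihood ratio).** Those figures assume an unadjusted model on 0/1 data with model-based variance. The document specifies neither 0/1 data nor the variance estimator, and adjustment is planned.

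**Conclusion.** The mismatch holds. The 30 patients and 80% power are right for an unadjusted, unpaired χ² test at 25% versus 75%, and that test is no declared end point and not the planned primary analysis. The within-patient objective has no stated size, power or precision.

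The fault lies in the justification and in the consistency of the primary end point; the documents do not show the number of patients to be too small. The roughly 87% at 48 hours rests on the cited 34% and 75% and on the assumed 12.5% low-risk value. It is sensitive to the overall added yield: at 20% or below, the chance of at least six new detections is 57% or less with 30 patients.

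**What to change.** Before data analysis, which the article says has not started:

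1. Use one primary end point in the Objective, Outcomes, Statistical Analysis and Results sections, in line with the stated objective: the within-patient added nsVT yield of 14 days over the first 48 hours. Keep 24 hours as a further comparison.
2. Justify 30 evaluable patients for it mainly by precision (8/30, 12% to 46%; pooled 14-day prevalence 15/30, 31% to 69%), and show a range of assumed added yields.
3. State that the 80% applies only to the unadjusted low- versus intermediate-risk χ² contrast at 25% versus 75%, and list that contrast as secondary.

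If the sponsor meant the risk-group contrast to be primary, the alternative is to declare it so and align the objective, end point and analysis with it.

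No extra patients are needed. The cost is a dated, documented clarification of the primary end point in a registered study with 26 of 34 patients already recruited, which is somewhat more than rewording. The 80% can then no longer be claimed for the main objective.

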### Outcomes

The rate of nsVT detection in the first 24 and 48 hours of monitoring versus the whole 14-day monitoring period will be compared. In addition, the prevalence of AF and other arrhythmias will be examined. Moreover, the results of the cMRI and, if applicable, the results of the genetic examination will be considered. The HCM Risk–SCD calculator score will be recalculated if new findings have occurred.

nsVT is defined as ≥3 consecutive ventricular beats at a rate of 120 beats per minute, lasting for <30 seconds [1]. AF is defined as atrial tachyarrhythmia lasting for >30 seconds [15]. The diagnosis of HCM is based on echocardiography; septum hypertrophy ≥15 mm in the absence of other causes of myocardial hypertrophy or septal or posterior wall thickness ratio >1.3 is required.

At the patients’ request, they will be informed about the rhythm-monitoring results and the resulting therapy changes after the ECG patch has been returned.

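### Confounder-adjusted logistic regression with an open-ended covariate list is too much for about 30 patients: odds ratios by LGE and genotype will tend to be inflated, and penalised estimation with a small fixed covariate set is a cheap remedy

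*Protocol article*

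**What the plan says.** All of the analysis rules stand in the Statistical Analysis section of the protocol article.

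- Adjustment: "Since this is a cohort study, all analyses will be adjusted for confounders, including, for example, age and sex". Age and sex are only examples, and no upper limit is given. On selection: "Potential confounders will be assessed from a clinical point of view before the statistical analysis is performed".
- Model: "Secondary end points regarding the prevalence of cardiac arrhythmias will be analyzed using logistic regression". In the Results section these are the end points on arrhythmia prevalence in patients with positive cMRI findings (more than 5% LGE) and in patients with a positive genetic diagnosis. The primary end point and the patient-count end points (AF detected, therapy changed) go to Poisson regression, with negative binomial regression as sensitivity analysis.
- Sample size: for low risk, "a prevalence of 25% after 14 days is assumed"; "In the intermediate-risk group, a prevalence of 75% is expected". A chi-square test then gives 30 evaluable patients, or 34 with 10% dropout.
- Comparison of monitoring windows (Outcomes): "The rate of nsVT detection in the first 24 and 48 hours of monitoring versus the whole 14-day monitoring period will be compared". The Objective and Discussion describe this as a comparison within the same patient.

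**The concern.** The adjustment rule has no exception and no limit on covariates, while the sample was sized for a two-group test without any. In small samples, maximum-likelihood logistic regression overstates odds ratios, and more so with each added coefficient. If a covariate pattern splits events from non-events completely (separation), there is no finite estimate at all.

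The results at stake are the associations of arrhythmia with LGE and genotype, which the Study Design section names as an aim. An inflated adjusted odds ratio could be read as stronger evidence than the data hold.

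The rule also covers the within-patient comparison, where age and sex are the same in both windows and have nothing to confound.

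**Working it through.** **1. The plan's sample size.** Inputs: 25% versus 75%, two-sided α = 0.05 (sidedness is not stated, but two-sided reproduces the figure), power 0.80.

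n per group = [1.96 × √(2 × 0.5 × 0.5) + 0.8416 × √(0.25 × 0.75 + 0.75 × 0.25)]² / 0.5² = (1.386 + 0.515)² / 0.25 = 14.5, so 15 per group and 30 in total. With dropout, 30 / 0.9 = 33.3, so 34. Both figures reproduce. Power at 15 per group is 0.816 by the normal approximation and 0.808 by exact enumeration. There is almost no slack and no allowance for covariates.

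**2. Events per coefficient at n = 30** (exposure + age + sex = 3 coefficients; four covariates = 5).

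- nsVT: 15 × 0.25 + 15 × 0.75 = 15 events and 15 non-events. 15 / 3 = 5.0; 15 / 5 = 3.0. At n = 34: 17 / 3 = 5.7.
- AF at the 23% cited in the Introduction for 24- to 48-hour Holter: 0.23 × 30 = 6.9 events. 6.9 / 3 = 2.3; 6.9 / 5 = 1.4.

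**3. Behaviour of the logistic fit.** Data sets were simulated with a binary exposure and covariates unrelated to exposure or outcome. Each was fitted by maximum likelihood, with a linear-programming check for separation. Inflation is the geometric mean odds ratio (OR) of the finite fits divided by the true one. Cells show share non-finite / inflation, n = 30.

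| Scenario | True OR | Exposure only | + 2 covariates | + 4 covariates |
|---|---|---|---|---|
| nsVT 25% vs 75% | 9.0 | 2.8% / 1.17 | 5.2% / 1.54 | 9.0% / 2.37 |
| Any arrhythmia 35% vs 65% | 3.4 | 0.4% / 1.10 | 1.2% / 1.28 | 2.4% / 1.49 |
| Any arrhythmia 43% vs 68%, 60% gene-positive | 2.8 | 0% / 1.11 | 1.4% / 1.27 | 2.2% / 1.49 |
| AF 13% vs 33% (mean 23%) | 3.3 | 12% / 0.89 | 17% / 1.04 | 22% / 1.32 |

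A second AF run gave 14%, 18% and 24% non-finite. With all 34 patients, inflation with two and four covariates is 1.44 and 2.03 (nsVT), and 1.18 and 1.40 (any arrhythmia, 35% vs 65%).

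Part of the average comes from nearly separated data sets with very large estimates. For nsVT the median log OR is 2.50 with two covariates and 2.75 with four, against a true 2.20, so the typical inflation is exp(0.30) = 1.35 and exp(0.55) = 1.73. In the gene scenario, the share of fits that are finite but more than double the true OR rises from 20% with no covariates to 29% with two and 35% with four.

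**4. Incomplete genetic testing.** Outcomes says genetic results are used where applicable, and the number tested is not given. If 20 were tested (an assumption), non-finite fits with two and four covariates are 7% and 16% for any arrhythmia, and 43% and 50% for AF.

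**5. Within-patient comparison.** In a log-link (Poisson) GEE on one simulated paired data set, the log ratio between windows was 2.793 with and without age and sex for counts, and 1.466 with and without for detection. Standard errors did not change.

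**6. Penalised alternative.** Under the same scenarios, Firth's penalty gives finite estimates, with average odds ratios close to the true value and error equal to or below that of maximum likelihood.

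**The case against.** A reader might infer that the planned logistic models will often yield no finite estimate. The documents do not support that. Logistic regression is assigned only to arrhythmia prevalence. At the plan's own rates nsVT alone affects about half of the patients, and non-finite fits are then uncommon. AF detection and therapy changes go to Poisson regression. Sparse groups matter there too: at 13% versus 33% the chance of no events in at least one group of 15 is 1 − (1 − 0.87¹⁵)(1 − 0.67¹⁵) = 13%. That is a separate matter from the logistic models. Nothing in the article gives a rate for arrhythmias rarer than AF.

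Nor is adjustment the main cause of separation. For AF, two covariates raise the non-finite share only from 12% to 17%; the rest comes from the sample size. Adjustment does add to the average inflation: 1.17 to 1.54 for nsVT, 1.10 to 1.28 for any arrhythmia.

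A reader might also infer that adjusting the within-patient comparison spoils it, or that a prevalence has nothing to adjust for. Step 5 shows redundancy, not bias. Risk group, LGE and genotype are between-patient exposures, for which adjustment is legitimate.

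Finally, covariate limits and estimation details are often left to the SAP, confounders are to be chosen before analysis, and the Results section presents these end points as exploratory. That lowers the weight of the point. It does not remove it, because the article itself fixes the model and an adjustment rule without limit, and a better method is available at almost no cost.

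**Conclusion.** The point holds in limited form, as a cheap improvement. For nsVT or any arrhythmia, the adjusted logistic odds ratios would be inflated on average about 1.2 to 1.5 times with two covariates and about 1.4 to 2.4 times with four. At n = 30 about 1% to 9% of fits would be non-finite. The non-finite share rises to about 17% to 24% if AF is modelled singly, and further if few patients have genetic results.

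These sizes rest on assumptions that the article does not supply: event rates by LGE and genotype (the nsVT row borrows the risk-group rates), half of patients exposed except in the gene scenario, covariates unrelated to exposure or outcome, and up to four covariates. The 60% gene-positive share and the 23% AF rate are from the Introduction. The primary within-patient result is not threatened.

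**What to change.** Change the Statistical Analysis wording before analysis begins:

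- For the between-patient associations with LGE and genotype, replace ordinary logistic regression with Firth-penalised logistic regression and profile-likelihood intervals.
- Fix at most one or two covariates in advance, such as age and sex, and report the unadjusted estimate alongside the adjusted one.
- Limit the adjustment statement to between-patient comparisons, and leave the 14-day versus 24- or 48-hour comparison as a paired analysis without covariates.

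The cost is a few sentences, with no new data or patients; the article reports that data analysis has not started. The downside is residual confounding by factors left out, which must be stated as a limitation. Penalisation removes most of the bias but not the imprecision of about 30 patients, so intervals will stay wide.

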## Discussion

This prospective study aims to measure the prevalence of nsVT in 34 patients with HCM observed by mHealth-based continuous rhythm monitoring over 14 days compared to standard practice (a 24- and 48-h long-term ECG). Thereby, the frequency of ventricular arrhythmias in the 14 days is compared with the frequency in the first 24 or 48 hours for the same patient (intraindividual comparison). We will evaluate whether the prolonged rhythm monitoring detects nsVT and AF more often compared to conventional 48-hour monitoring and to what extent these findings can induce changes in therapeutic management. It may be speculated that, especially in patients with intermediate HCM Risk–SCD calculator scores, prolonged monitoring may identify patients at high risk, who may potentially benefit from a prophylactic ICD, with higher accuracy. If no rhythm abnormality is detected during the 14-day monitoring, this will not likely occur in everyday life and ICDs can be avoided due to a sufficiently low risk. In addition, a higher diagnostic yield for previously undetected AF may also improve decision-making regarding the need for early anticoagulant therapy.

We set an upper age limit of 75 years because it is known that especially young patients with HCM especially have a higher risk of SCD [13]. Nevertheless, a residual risk remains, so no upper limit for ICDs is defined in the European Society of Cardiology guidelines. Several years ago, the DANISH (The Danish Study to Assess the Efficacy of ICDs in Patients With Nonischemic Systolic Heart Failure on Mortality) study demonstrated no survival benefit from an ICD in patients older than 75 years in a sample of patients with systolic heart failure [18]. We have followed this age limit despite the different patient samples.

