We hypothesize that prolonged rhythm monitoring will detect more arrhythmias than 24- or 48-hour monitoring. In a study with prolonged rhythm monitoring by Holter ECG over 14 days, 75% of patients with HCM had nsVT, compared with only 16.9% of patients in the first 24 hours [6]. However, it remains unclear if all these patients with nsVT should now receive an ICD. Previous studies have shown that patients who present with nsVT during 24-hour monitoring show it more frequently if monitoring is prolonged. Patients who showed nsVT later in the subsequent 14 days usually had only one episode [7]. Thus, it can be speculated that the detection of nsVT in a 24-hour monitoring period indicated more frequent spells of nsVT overall, with an associated higher SCD risk. Moreover, the rate and duration of nsVT vary, suggesting that longer and more rapid nsVT episodes indicate a higher SCD risk [6]. Prolonged monitoring may allow for the identification of patients with more frequent nsVT episodes, also taking into account the rate and duration of nsVT.

In addition, a correlation with late gadolinium enhancement load on cMRI will be investigated. If patients with high late gadolinium enhancement load show increased nsVT, these scar areas detected on cardiac MRIs could be identified as possibly pathogenic for the arrhythmias, and appropriate therapy (eg, ICD fitting) should be performed. This has so far not been investigated, so the results are needed.

In addition, the mHealth ECG patch method used here offers opportunities for other diseases as well. For example, patients with a stroke of unclear origin can be screened for AF over an extended period. It is also possible to capture intermittent subjectively perceived cardiac arrhythmias with the help of such an ECG patch, as this is often not possible with normal long-term ECGs.

In summary, prolonged mHealth-based rhythm monitoring will be used to investigate arrhythmia burden in patients with HCM. Increased detection of arrhythmias compared with 24-hour long-term ECG monitoring can be expected. It is essential to individually consider the rhythm monitoring results and optimize therapy accordingly. Findings of prolonged rhythm monitoring might be helpful in cases of borderline risk. A thorough discussion of the findings and possibly individual reassessment using the risk calculator could be an approach.

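### The stated primary analysis, a Poisson regression, has no feature for the paired, nested comparison of 24/48 hours with 14 days and does not estimate the added detection

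*Protocol article*

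**What the plan says.** The Outcomes section opens with the comparison itself: "The rate of nsVT detection in the first 24 and 48 hours of monitoring versus the whole 14-day monitoring period will be compared". The Discussion describes the comparator as "the frequency in the first 24 or 48 hours for the same patient (intraindividual comparison", and the Objective in the Abstract says the same. The Discussion gives the hypothesis: "We hypothesize that prolonged rhythm monitoring will detect more arrhythmias than 24- or 48-hour monitoring".

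The Results section words the primary end point differently: "The primary study objective and primary end point is the prevalence of nsVT in patients with HCM at low to intermediate risk". That is a yes/no outcome per patient.

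The Statistical Analysis section then states: "A Poisson regression will be applied to analyze the primary end point (rate of nsVT detection". It continues: "Furthermore, we will conduct a negative binomial regression as a sensitivity analysis". It also says that all analyses will be adjusted for confounders such as age and sex, because this is a cohort study. It mentions no exposure term, no patient-level term and no clustered variance, and it does not say which contrast the Poisson model estimates.

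The sample size in the same section is for another contrast, low against intermediate risk at 14 days by a chi-square test: "Therefore, a prevalence of 25% after 14 days is assumed" for low risk, and "In the intermediate-risk group, a prevalence of 75% is expected [6" for the other group.

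**The concern.** The first 24 or 48 hours are part of the same 14-day recording in the same patient, so the two windows are paired and one lies inside the other. The components named in the plan suit independent patients. Age and sex are the same in both windows of one patient, so adjusting for them does nothing for this contrast. A negative binomial model addresses overdispersion of counts, not pairing, and has no clear role for a yes/no outcome.

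The quantity the study needs is the number of patients found only because monitoring went on. The stated model does not target it, and the result would depend on choices the article does not fix: episode counts or yes/no detection, offset or none, clustered variance or not. Neither 24 nor 48 hours is named as the primary comparator, and the size of the problem differs between them.

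**Working it through.** **The plan's own figure.** For 25% against 75%, two-sided α = 0.05 and power 0.80, without continuity correction:

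n per group = [1.960·√(2·0.5·0.5) + 0.842·√(0.25·0.75 + 0.75·0.25)]² / 0.5² = 14.5, rounded up to 15.

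The total is 30, and 30/0.9 = 33.3, rounded up to 34. The stated size reproduces. It is for the risk-group contrast at 14 days, not for the window comparison.

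**Inputs for the window comparison** (30 evaluable patients, 15 per risk group):
- 14 days: 25% low risk, 75% intermediate (Statistical Analysis).
- 48 hours, intermediate: 34% (cited study, Introduction), or 37.5% if the plan's doubling is applied to 75%.
- 48 hours, low risk: 12.5%. This is an assumption, half of 25% by the same doubling; the studies the plan cites for low-risk patients range from 7% to 42% at 24 to 48 hours.
- 24 hours, intermediate: 16.9% (cited study, Discussion).
- 24 hours, low risk: not given; varied from 6.25% to 12.5%.

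**Yes/no detection.** Let x₁₄ and xₛ be the numbers positive in 14 days and in the short window. Every short-window positive is also a 14-day positive.
- Poisson on independent rows: SE of the log ratio = √(1/xₛ + 1/x₁₄).
- Patient-clustered: SE = √(1/xₛ − 1/x₁₄), before small-sample correction.
- Exact McNemar: with d = x₁₄ − xₛ newly detected and none lost, p = 2·0.5^d. It falls below 0.05 from d = 6 (0.031; d = 5 gives 0.063).

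Example with 15/30 positive at 14 days and 7/30 at 48 hours, log ratio ln(15/7) = 0.762:

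| Method | SE | p |
|---|---|---|
| Poisson, independent rows | √(1/7 + 1/15) = 0.458 | 0.096 |
| Poisson, patient-clustered | √(1/7 − 1/15) = 0.276; 0.283 with the software's small-sample correction | 0.007 |
| Exact McNemar, d = 8 | – | 0.008 |

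Simulated power, drawing the short-window positives as a subset of the 14-day positives:

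| Comparison with 14 days | Poisson, independent rows | Exact McNemar |
|---|---|---|
| 48 h: low 12.5%, intermediate 34% | 28% | 87% |
| 48 h: low 12.5%, intermediate 37.5% | 20% | 81% |
| 24 h: low 12.5%, intermediate 16.9% | 77% | 99% |
| 24 h: low 6.25%, intermediate 16.9% | 87% | 99% |

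**Episode counts.** Counts were simulated as gamma-Poisson with a constant daily rate within each patient. Matching 16.9% at 24 hours and 75% at 14 days gives mean 0.202 per day and shape 1.075: 1 − (1 + 0.202/1.075)^−1.075 = 0.169 and 1 − (1 + 14·0.202/1.075)^−1.075 = 0.75.
- Without an offset, the median 14-day to 24-hour ratio is 14.25, and the independent-rows test rejects in 99.6% of runs although the daily rate never changes.
- With a log-time offset, the median rate ratio is 1.02 and rejection is about 2%, although detection rises by 75 − 16.9 = 58.1 points.

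This cohort uses the cited study's rates for all 30 patients, so it is not the mixed-risk cohort of the power table. Lower detection (50% at 14 days, 10% or 16.9% at 24 hours) gives the same pattern: ratios of 14.0 to 14.25 without an offset and 1.00 to 1.02 with one.

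**The case against.** The article says only that a Poisson regression will be used. It does not say that rows are treated as independent, and it calls the comparison intraindividual, so the authors know it is paired. Offsets and variance structure are often left to an analysis plan, which is not shown. This stands to the extent that one cannot say the planned fit is an unpaired one. It does not remove the point: the article commits to a model, a sensitivity model and an adjustment strategy, and none of these addresses pairing or yields the added detection.

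The model could also be meant for low against intermediate risk, where nesting does not arise and where adjustment for age and sex makes sense. The wording points the other way, since Outcomes and Statistical Analysis both speak of the rate of nsVT detection. If the risk-group reading were right, the stated objective would have no analysis, and the section would still need correcting.

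Four stronger readings are tempting and not supported:
- That Poisson regression cannot be used. With patient-clustered variance it gives p = 0.007 in the example, next to 0.008 for McNemar, and the article does not exclude it.
- That most of the power is lost whichever window is used. That holds for 48 hours. At 24 hours the loss is about 12 to 22 points, and at the cited 16.9% against 75% in all patients it nearly vanishes (99% against about 100%).
- That the fixed direction of the result is a fault of Poisson. Fourteen days cannot detect fewer patients than their own first hours under any test, McNemar included. The power figures therefore show how far the standard error is inflated; they do not make a test of no difference informative.
- That false positives threaten. On yes/no data, ignoring the pairing is conservative.

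**Conclusion.** The point holds in limited form. The stated primary analysis has nothing that handles the nested, within-patient comparison set as the objective, and none of its likely implementations reports the added detection directly. On yes/no data, independent rows would cut power from 81–87% to 20–28% at 48 hours and from 99% to 77–87% at 24 hours. On counts, the ratio is about 14 without an offset and about 1 with one, whatever the gain in patients detected.

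The figures assume 30 evaluable patients, low-risk short-window rates inferred from the plan's doubling or varied over 6.25% to 12.5%, and, for counts, a constant daily rate within each patient. The 48-hour result matters most because the Discussion treats 48-hour monitoring as the conventional comparator.

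**What to change.** In the Statistical Analysis section:
- Make the primary analysis of the window comparison the proportion of all evaluable patients whose first nsVT occurs after hour 48, with an exact 95% confidence interval overall and by risk group. Give 24 hours as the secondary window. For scale, 8 newly detected of 30 is 26.7%, exact interval about 12% to 46%.
- If a p-value or an adjusted ratio is wanted, use exact McNemar or Poisson with patient-clustered (GEE or robust) variance, and note that the nesting fixes the direction.
- If episode burden is compared, use non-overlapping windows (0 to 48 hours, and 48 hours to the end of recording) with a log-time offset and a patient-level term.
- State that the 34 patients were calculated for low against intermediate risk at 14 days, not for this comparison.

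A minimum worthwhile yield and a curve of time to first nsVT would be useful but are optional.

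The cost is a change of analysis wording. The continuous recordings already carry the times, and the article reports that data analysis has not begun, so the change can still be specified in advance.
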